- There is a plan for an upgrade of NIRS monitors to have neonatal pulse oximetry incorporated which will collect data on pulse oximetry (SpO2) and heart rate (HR). If this upgrade is available at the time of commencement of the study, data for SpO2 and HR will be downloaded simultaneously using the previously mentioned software. If this is not available, then we will collect data on SpO2 and HR from a Masimo devices or a similar pulse oximetry device (which are used routinely in NICUs to monitor pulse oximetry). The clocks on both devices (NIRS and Masimo) will be synchronised prior to commencement of monitoring for every patient that is enrolled. Data from Masimo pulse oximeters will be downloaded using a software program into CSV format. This data will be read by local PI and then by the central reporting team at Westmead Hospital. Data will be transferred using secure work-based email or Accellion App or secure file transfer platforms as approved by the local health authorities. File will be coded by the local PI; central reporting team will have de-identified version of the file. ICM+ software program will be used at 4 sites (US, New Zealand, Nepean and RHW) for centralised physiological data collection from the NIRS and the bedside clinical monitors. Westmead site has a similar software program (iXcellence) already in clinical use. Both these softwares offer identical data collection and ability to transfer data to CSV format for ease of statistical analysis. For the US site, NONIN NIRS monitors will be used for collection of primary outcome data. Other physiological data (for some aspects of secondary analysis) will be obtained when technical issues with ICM+ installation and connectivity have resolved.

- Other physiological functions (blood pressure): This data will be collected from medical records and the response to alarm form. File will be coded by the local PI; central reporting team will have de-identified version of the file.

B. Cerebral imaging (cranial ultrasound and MRI brain): Cranial ultrasounds are routinely performed for all premature babies at regular intervals. All ultrasounds and MRI brain are routinely reported by an independent radiologist. De-identified images will be transferred by the local PI to the central reporting team (Neuro-radiologists [name]) using an electronic file transfer system approved by local health authority.

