| Cranial imaging                                                                          | At regular intervals over the duration of admission                                                                                                                                    |  |                             |                                                                                                |
| Physiological function monitoring (pulse oximetry, recording heart rate, blood pressure) | Heart rate, pulse oximetry is recorded continuously, blood pressure intermittently using blood pressure cuffs or invasively if there is an arterial catheter when clinically indicated |  |                             |                                                                                                |
| Mortality and morbidity data                                                             | Entire duration of admission                                                                                                                                                           |  |                             |                                                                                                |
| Motor performance                                                                        | At 32 week and 36-37                                                                                                                                                                   |  |                             |                                                                                                |

|                                |                                                     |
|--------------------------------|-----------------------------------------------------|
| assessment                     | weeks PMA                                           |
| Neuro-developmental assessment | At regular intervals until 5 years after discharge. |

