#### Blinding (masking)

During intervention period: Due to the nature of the study, the assignment of infants to control arm or intervention arm cannot be blinded to the clinical staff (care providers). For infants in the control arm, the monitor screen will be blinded to the clinical team, this will be performed using an opaque cover over the monitor screen. For each monitor, it is possible to silence the low and high alarm, but keep the alarm ON for displacement of the sensors when the sensors are not making contact with the skin. Alarms for the range of cerebral tissue oxygenation (65-90) will be turned off and alarms for displacement/dislodgement of the sensors will remain active. Clinical staff (bedside nurse) will be provided with data collection sheet to determine the frequency of alarms and sensor repositioning during each shift for both arms.

Post-intervention period: Data analysts, other site personnel/investigator, outcome assessors and manuscript writers will be blinded to the intervention.

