**Adherence**

In response to an alarm (for intervention and control group), an event will be marked by the bedside clinical team on the NIRS monitor. From the Response To Alarm form, NIRS data and medical records observation chart, we will ascertain adherence to the study algorithm and

actions performed. Research nurse/local PI will conduct compliance audit for both groups during the study.

For the intervention group: A bedside “Response to Alarm” form will be made available for staff to prospectively record actions performed for low &/ high cerebral oxygenation alarms during their shift to ensure compliance to the clinical algorithm as well as event mark in response to the alarm on the NIRS monitor.

Nursing and medical staff will receive education prior to study commencement on the application of NIRS sensors, skin care during monitoring period, measures to consider when there is cerebral hypoxia and/or cerebral hyperoxia. Bedside flowcharts will be available for staff to perform changes to clinical management. A laminated chart will be placed on the crib to remind staff of NIRS target range as well as a flow chart suggesting possible reasons for cerebral hypoxia/hyperoxia and suggested interventions.

For the control group: A bedside “Response to alarm” form will be made available for staff to record prospectively actions performed for sensor contact alarms during their shift to report accuracy and vigilance of recordings as well as place an event marker in response to the poor patient contact alarm on the NIRS monitor. We will have a laminated chart specifying treatment ‘as per medical officer’s instructions’ for the control group.

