### *Secondary outcomes*

- Newborn mortality rates prior to home discharge
- Brain injury based on cerebral imaging prior to home discharge
- Neonatal morbidities (chronic lung disease, necrotizing enterocolitis, retinopathy of prematurity) prior to home discharge

- Physiological functions (observation of pulse oximetry) at 36-37 weeks PMA.
- Sleep architecture (based on sleep study) at 36-37 weeks PMA.
- Motor performance assessment (General movements assessment) during NICU stay and at 4 months corrected age follow up.
- Neuro-developmental outcomes until 5 years of age.
- Measurement of physiological functions (heart rate, pulse oximetry, blood pressure) in the first 5 days.

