### *Analysis of the outcomes*

Participant demographic and clinical characteristics and study outcomes will be presented using standard descriptive statistics: frequencies and percentages for categorical variables, mean, standard deviation and range or median, quartiles and range for continuous variables. All efficacy analyses will be performed according to randomized treatment. We will use a suitable transformation to ensure normality for the primary outcome, the burden of cerebral hypoxia and hyperoxia and use generalized estimating equation (GEE) or a similar method for comparison between groups. Sub-group analysis for stratification variables will be performed. For reporting the burden of cerebral hypoxia and hyperoxia, we will include deviations in cerebral oxygenation more than a minute. This pragmatic approach will ensure we achieve a balance between responding to an alarm from poor sensor contact with the participant and identifying true real-time changes in cerebral oxygenation. To allow comparison of the primary outcomes with other studies, we will also report the burden of cerebral hypoxia and hyperoxia more than 10 minutes. Other study outcomes will be compared using similar methods, using GEE methods with normal or binary outcome distribution and correlation between outcomes in twins. Adjusted models will explore predictors out outcomes. No corrections for multiple hypotheses will be performed. Adjusted models will be used to explore predictors of outcomes. Variables that differed significantly between the two groups, and could plausibly contributory to the outcome, will be considered for adjustment. A fixed adjustment for gestational age category will be included as an a priori specified variable. For this trial, no imputation of missing data will be performed and sensitivity analysis will only be performed separately for the burden of cerebral hypoxia and cerebral hyperoxia. In future, sensitivity analysis may be performed for variables such as specific gestational age or treatment received.

Withdrawn participants will be replaced in the study with new randomisation (per protocol). To facilitate and ensure long term follow up, existing measures which are standard practices includes providing appointment letters by post, reminding and confirming with families by phone and/or text message when follow up appointment is close to date.

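### The between-arm comparison of first-5-day blood pressure is open to bias, because one named source is a form triggered by different events in the two arms

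*Combined protocol and SAP*

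**What the plan says.** **Outcome.** Protocol 5.4 places blood pressure among the exploratory secondary outcomes, and the SAP (Secondary outcomes) repeats it: "Measurement of physiological functions (heart rate, pulse oximetry, blood pressure) in the first 5 days". The SAP (Analysis of the outcomes) states: "Other study outcomes will be compared using similar methods, using GEE methods with normal or binary outcome distribution". Protocol 5.3 also has an objective relating cerebral hypoxia and hyperoxia to blood pressure over the same days.

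**Source.** For blood pressure, protocol 6.2 item 5A says: "This data will be collected from medical records and the response to alarm form". The outcomes table in protocol 6.5 gives the tools for SpO2, heart rate and blood pressure as the pulse oximeter and medical records. It does not mention the form.

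**When the form is completed.** Protocol 6.5 (Adherence) provides a form in both arms, with different triggers. Intervention-arm staff are to "prospectively record actions performed for low &/ high cerebral oxygenation alarms during their shift". Control-arm staff are to "record prospectively actions performed for sensor contact alarms during their shift". For control infants, protocol 6.4 (Blinding) says: "Alarms for the range of cerebral tissue oxygenation (65-90) will be turned off". Their sensor-displacement alarms stay on.

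**Routine measurement.** The standard-care table in protocol 6.3 describes "blood pressure intermittently using blood pressure cuffs or invasively if there is an arterial catheter when clinically indicated".

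**The concern.** A between-arm comparison needs the outcome to be sampled in the same way in both arms. Used as written, item 5A adds readings tied to a cerebral deviation in one arm and readings tied to a loose sensor in the other.

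The protocol itself connects these deviations to blood pressure. Figure 1 in 6.5 lists systemic hypotension among the causes of low cerebral oxygenation and includes blood pressure among the checks. Figure 2 lists systemic hypertension among the causes of high cerebral oxygenation. Form readings in the intervention arm may therefore be enriched for abnormal values in a way that control-arm form readings are not.

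At stake is a circulatory measure in a trial whose treatment algorithm acts partly on the circulation. A sampling artefact could look like harm or hide a benefit.

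**Working it through.** **1. Does the plan remove the difference in sampling?** The sections read together as follows.

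| Question | Intervention arm | Control arm |
|---|---|---|
| Is the form a blood pressure source? (6.2 item 5A) | Yes | Yes |
| What triggers the form? (6.5 Adherence) | Low or high cerebral oxygenation alarm | Sensor-contact alarm |
| Are the 65-90% range alarms on? (6.4; SAP Blinding) | Yes | No |
| Does a study algorithm prompt a blood pressure check during a deviation? (6.5 Figure 1) | Yes | No |
| Is the form listed in the outcomes table? (6.5) | No | No |

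Neither the protocol nor the SAP defines the per-infant blood pressure summary, fixes reading times, weights readings by time, or says how form and chart readings are combined. The planned GEE handles correlation between twins, and the SAP adds an adjustment for gestational age category. Neither corrects for readings taken at different kinds of moment in the two arms.

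**2. Can the size be computed?** No. The documents give no number of form readings, no routine reading frequency and no blood pressure shift during deviations.

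**3. Illustration on assumed values.** Only the sample size and design effect come from the plan, so these are reproduced first.

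- Difference 0.3, SD 0.5, two-sided 5%, 80% power: the t-based calculation gives 44.6, so 45 per arm. The normal approximation gives 44.
- Design effect: 1 + (1.3 − 1) × 0.1 = 1.03.
- 45 × 1.03 = 46.35, rounded up to 47 per arm, 94 in total. The plan's figure reproduces.

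Now suppose there is no true difference and the outcome is each infant's mean over all readings. Let f be the share of intervention-arm readings that come from deviation alarms. Let d be the shift in blood pressure at those times, in between-infant SDs and all in one direction. Assume that control-arm form readings are unshifted.

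- Bias = f × d
- SE = √(2 × 1.03 / 47) = 0.209 SD
- False-positive rate = Φ(bias/SE − 1.96) + Φ(−bias/SE − 1.96)

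| f (assumed) | d (assumed) | Bias (SD) | False-positive rate |
|---|---|---|---|
| 0 (form not used) | any | 0 | 5.0% |
| 10% | 0.25 | 0.025 | 5.2% |
| 25% | 0.5 | 0.125 | 9.2% |
| 50% | 0.5 | 0.25 | 22% |
| 50% | 1.0 | 0.5 | 67% |

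The table shows how the problem scales. It does not show where this trial would fall.

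**4. What is unaffected?** The primary outcome comes from the NIRS device download. SpO2 and heart rate come from device or monitor downloads (6.2 item 5A). None of them depends on the form.

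**The case against.** The strongest reply is that item 5A says where blood pressure data are collected, not that form readings enter the between-arm summary. The Adherence section describes the form as a record of actions and uses it to check compliance, and the outcomes table leaves it out. If form values only duplicate readings charted on a common schedule, or serve only to describe alarm episodes, the form adds no bias. This stands. A reader might infer that the comparison is biased, or that the intervention arm will show more hypotension and hypertension; the documents support neither. Open to bias is as far as they go.

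The direction is also uncertain. Figure 1 names several causes of low cerebral oxygenation besides hypotension, and sensor misplacement is another possibility. Effects at low and high alarms could partly cancel in a mean. The documents do not say whether a form reading is taken before or after corrective action.

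A reader might also infer that control infants have no form. They do; what differs is the trigger.

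Finally, readings taken during deviations are relevant to the objective relating cerebral oxygenation to blood pressure, so discarding them altogether would lose information. Excluding alarm-prompted readings from the chart could also select differently by arm, since range-alarm prompts occur only in the intervention arm, and the documents do not say that charts identify prompted readings. Both points stand and shape the fix.

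The objection does not remove the gap. One section names the form as a source, another omits it, and nothing says which governs the comparison.

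**Conclusion.** The point holds in limited form. As written, a stated source of an outcome compared between arms is triggered by cerebral deviation in one arm and by loss of sensor contact in the other, and the plan contains nothing to neutralise this. The form-related bias depends on two things the documents leave open: whether form readings enter the between-arm summary, and how far blood pressure differs at alarm times. Its size and direction are therefore unknown. The range from 5.2% to 67% rests wholly on assumed f and d and should not be read as an estimate for this trial.

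The consequence is confined to one exploratory secondary outcome. It would be wrong to infer that the primary comparison or the sample size is in doubt. The case for acting is that the correction is cheap and an uncorrected result would be hard to interpret.

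**What to change.** 1. Reconcile protocol 6.2 item 5A with the outcomes table in 6.5 by removing the Response to Alarm form as a source for the between-arm blood pressure outcome.
2. In the SAP, define one per-infant blood pressure summary for both arms, taken from the routine chart or monitor record at the same pre-set clock times. One workable rule is the reading nearest each fixed time point, chosen in the same way in both arms whether or not it was prompted. Where continuous monitor data include blood pressure, a time-weighted summary would serve. Item 5A describes centralised monitor collection but does not name blood pressure in it, so availability would need confirming.
3. Keep form readings for adherence and for within-infant description of deviation episodes, and state that use.

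**Cost.** A wording change to the protocol and SAP, with no new measurements. Some form readings are not used in the between-arm comparison. Some asymmetry may remain, because the hypoxia algorithm can prompt extra charted readings in the intervention arm and these may fall nearest a clock time. The common rule reduces this without guaranteeing its removal.

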## 6.3 STANDARD CARE AND ADDITIONAL TO STANDARD CARE PROCEDURES

| Standard Care Procedures                                                                 |                                                                                                                                                                                        |  | Additional To Standard Care |                                                                                                |
|------------------------------------------------------------------------------------------|----------------------------------------------------------------------------------------------------------------------------------------------------------------------------------------|--|-----------------------------|------------------------------------------------------------------------------------------------|
| Procedure                                                                                | Time/Visit                                                                                                                                                                             |  | Procedure                   | Time/Visit                                                                                     |
| Skin assessment                                                                          | Entire duration of admission                                                                                                                                                           |  | NIRS monitoring             | First 5 days (for intervention) and at 36-37 weeks PMA (for observation only with sleep study) |
|                                                                                          |                                                                                                                                                                                        |  | Day sleep study (once)      | At 36-37 weeks PMA.                                                                            |
| Cranial imaging                                                                          | At regular intervals over the duration of admission                                                                                                                                    |  |                             |                                                                                                |
| Physiological function monitoring (pulse oximetry, recording heart rate, blood pressure) | Heart rate, pulse oximetry is recorded continuously, blood pressure intermittently using blood pressure cuffs or invasively if there is an arterial catheter when clinically indicated |  |                             |                                                                                                |
| Mortality and morbidity data                                                             | Entire duration of admission                                                                                                                                                           |  |                             |                                                                                                |
| Motor performance                                                                        | At 32 week and 36-37                                                                                                                                                                   |  |                             |                                                                                                |

|                                |                                                     |
|--------------------------------|-----------------------------------------------------|
| assessment                     | weeks PMA                                           |
| Neuro-developmental assessment | At regular intervals until 5 years after discharge. |

#### 6.4 RANDOMISATION

Central randomisation can be performed by the investigator or by a delegate or by the medical team member (from NICU). Infants assessed as eligible will be randomised to control group or intervention group using variable block randomisation stratified for gestation age (< 26 weeks and ≥ 26 weeks) and study site using web based secure software (REDCap). Randomisation codes for the study will be generated by biostatistician ([name] has generated the codes). Permuted blocks will maintain group balance, infants will be allocated to two groups in a 1:1 ratio. Multiple births (twins) will be assigned to the same arm of the treatment (either intervention or control). Multiple births (twins) will be randomised to the same group, based on negligible intra-class coefficient (ICC) burden of hypoxia within pairs of twins in SafeBoosC-II study (16) and survey of parents of multiple births (19).

To ensure concealment, the block sizes will not be disclosed. Additionally, allocation concealment will be ensured, as REDCap will not reveal the randomisation until the infant has been recruited into the trial.

REDCap will maintain a list of participants enrolled. Each site PI will access only to their site records. The chief investigators will have access to all sites to oversee enrollment. Participants will be given unique codes to protect their identity on all documentation utilised for recording and analysis purposes. Separate data records will be maintained for re-identifiable and de-identified data.

